### Duration

The total duration of the trial is 4 weeks. The trial will run parallelly across all six zones. The expected duration of involvement of each participant is 1 month.

### Recruitment of participants within PIAs

We will recruit 120 passed out youth from each participating PIA (total= 1440). All participants from one PIA will be either in the intervention arm or control arm. The participants are aged between 18 and 35, of all genders, and upskilled in different domains. Participants will be invited to take part in baseline assessment and intervention programmes.

#### Inclusion criteria

Alumni students of the DDU-GKY programme who are either working or are in search of a jobOwn a smartphone

#### Exclusion criteria

Do not possess a smartphoneUnable to operate a smartphoneReceipt of treatment for pre-existing mental health conditions in the last year

### Randomisation and blinding

Following the completion of the baseline assessment for all participants, the eligible participants will be randomised at a 1:1 ratio to one of the two arms (intervention or control) by the trial manager based on the PIA to which they belong. A computer technician will create a computer-generated random number list, and odd numbers on the list will be allocated to the intervention arm, and the even numbers will be allocated to the control arm.

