### Design

Cluster randomised controlled trial

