### Study location

The entire country of India, comprising 29 states, is further divided into six geographical zones and decided to include PIAs representing each zone, in consultation with the Director of National Institute for Rural Development and Panchayat Raj (NIRDPR), training head and her team. This clustering was done to capture the sociocultural and economic variations in settings and population and to address the needs specific to each zone. Table 1 lists the states that fall under each zone. 771 DDUGKY project-implementing agencies are functioning in India, spread across the different states in each of the zones. The number of PIAs within each state varies, 8 being the lowest and 160 being the highest. A list of PIAs in each zone will be prepared, and 12 PIAs will be randomly selected from each zone.

**Table 1 Tab1:** List of states that fall under each zone

Geographical zones	States in the zone
1. Northern zone	Delhi, Himachal Pradesh, Jammu and Kashmir, Punjab, Uttarakhand, Uttar Pradesh
2. North-East zone	Assam, Arunachal Pradesh, Manipur, Meghalaya, Mizoram, Nagaland, Sikkim, Tripura
3. Central zone	Madhya Pradesh, Chattisgarh
4. Eastern zone	Bihar, Jharkhand, Odisha, West Bengal
5. Western zone	Goa, Gujarat, Maharashtra
6. Southern zone	Andhra Pradesh, Karnataka, Kerala, Puducherry, Tamil Nadu, Telangana

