### Recruitment of clusters (PIAs)

Two project-implementing agencies (PIA) will be recruited from each of the six zones (12 PIAs in total). For a PIA to be included in this study, it should be in one of the six zones and be an active, currently operational PIA with a full-time staff. A list of eligible PIAs will be prepared, and NIRDPR will use a computer-generated randomisation procedure to select the PIAs in the six zones. The NIRDPR will contact only those agencies meeting the inclusion criteria and invite them to participate in the study. This process will be continued till 12 consenting PIAs are selected for the project implementation. Six of the selected PIAs will be allocated to the intervention arm, and 6 PIAs will be allocated to the control arm. The state monitoring agencies will collect information on the number of full-time staff and contact details of students who completed their courses.

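### The odd/even rule ignores the two-PIAs-per-zone design and does not by itself secure six PIAs per arm; one draw within each zone would guarantee both at no cost

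*Protocol article*

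**What the plan says.** The Design section gives the design as "Cluster randomised controlled trial". Under Recruitment of clusters (PIAs), the article states "Two project-implementing agencies (PIA) will be recruited from each of the six zones (12 PIAs in total") and then "Six of the selected PIAs will be allocated to the intervention arm, and 6 PIAs will be allocated to the control arm". Study location gives the reason for working by zone: "This clustering was done to capture the sociocultural and economic variations in settings and population and to address the needs specific to each zone". Recruitment of participants within PIAs sets 120 participants per PIA, 1440 in all, and keeps each PIA in a single arm. The Intervention section lists 720 per arm.

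The mechanism appears only under Randomisation and blinding. Allocation follows completion of baseline, the ratio is 1:1, and a technician generates the numbers by computer. The rule applied to them is: "odd numbers on the list will be allocated to the intervention arm, and the even numbers will be allocated to the control arm". No section of the text mentions stratifying, pairing or blocking by zone, and none says whether the list is a set of free random numbers or a shuffle of 1 to 12.

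Study location also says that "12 PIAs will be randomly selected from each zone", which would give 72 PIAs. The Abstract, the cluster recruitment section and the total of 1440 all agree on 12 overall, and that figure is used here.

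**The concern.** The selection stage builds six natural pairs because the zones are expected to differ. The allocation stage then makes no use of them. Two properties that the rest of the plan relies on are therefore left to chance, or to an unstated feature of the list:

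- **Six PIAs per arm.** Training of the staff is planned for six intervention PIAs reaching 720 alumni, and the sample size section assumes 720 per arm. Parity secures this only if exactly half the numbers used are odd.
- **Balance of zones between arms.** With six clusters per arm, a zone with both PIAs in the same arm puts its own average level into the arm difference and offers no within-zone comparison. This cannot be repaired after allocation.

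**Working it through.** **Inputs from the article.** 6 zones, 2 PIAs per zone, 120 participants per PIA, 6 PIAs per arm, and allocation by parity.

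**The plan's own figures.** 6 × 2 = 12 PIAs; 12 × 120 = 1440; 6 × 120 = 720 per arm. These reproduce. The stated 80% power cannot be reproduced, because the article gives no effect size, SD or intracluster correlation (ICC).

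**Reading A: each PIA's number is odd or even independently, probability 1/2.** There are 2^12 = 4096 equally likely allocations.
- Exactly 6:6: C(12,6)/4096 = 924/4096 = 22.6%.
- 8:4 or more uneven: 2 × [C(12,0)+…+C(12,4)]/4096 = 2 × 794/4096 = 38.8%.
- All six zones split: (1/2)^6 = 1.6%, so at least one zone is unsplit in 98.4%. The expected number unsplit is 6 × 1/2 = 3.

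**Reading B: the list is a permutation of 1 to 12, so 6:6 is forced.** There are 924 allocations.
- All six zones split: 2^6/924 = 64/924 = 6.9%, so at least one zone is unsplit in 93.1%.
- Expected unsplit zones: once one PIA of a zone is placed, 5 of the other 11 share its arm, giving 6 × 5/11 = 2.73.

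| Unsplit zones | Allocations | Probability |
|---|---|---|
| 0 | 64 | 6.9% |
| 2 | 480 | 51.9% |
| 4 | 360 | 39.0% |
| 6 | 20 | 2.2% |

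**What an unsplit zone does.** Let zone averages vary with SD τ (an assumption; the article gives no value). With six PIAs per arm, each unsplit zone adds ±2/6 of its effect to the arm difference. For k unsplit zones the added SD is τ × √(4k)/6:
- k = 2: 0.47 τ
- k = 4: 0.67 τ
- k = 6: 0.82 τ
- every zone split: 0

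**One draw within each zone.** There are 2^6 = 64 allocations. Each gives 6:6, 720:720 and one PIA per arm in every zone.

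**Does fitting zone as a fixed effect then gain power?** Assume a cluster-level comparison, two-sided 5% and 80% power from the non-central t. In SD units the variance of the difference is 2 × [ICC × (1 − s) + (1 − ICC)/120]/6, where s is the share of between-PIA variance explained by zone. The unpaired analysis has s = 0 and 10 df; the zone-adjusted analysis has 5 df. Neither ICC nor s is in the article.

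| Assumed ICC | Unpaired, 10 df | Zone fitted, s = 0 | s = 10% | s = 50% | Break-even s |
|---|---|---|---|---|---|
| 0.01 | 0.24 | 0.27 | 0.27 | 0.23 | 40% |
| 0.02 | 0.30 | 0.34 | 0.33 | 0.27 | 31% |
| 0.05 | 0.43 | 0.49 | 0.47 | 0.37 | 25% |

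Entries are detectable differences in SD units. The zone term helps above the break-even share and costs power below it.

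**The case against.** The strongest reply is that unrestricted cluster randomisation is valid: over repeated allocations the arm comparison is unbiased. That stands. A reader might infer from the 93% figure that arm will probably be confounded with zone, and the documents do not support that. The figure counts any unsplit zone. With 6:6, unsplit zones come in equal numbers to each arm and may partly offset each other. All six are unsplit in only 2.2% of allocations (1.6% under independent parity).

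Second, the article says six and six, 720 and 720, and 1:1, and a shuffled list of 1 to 12 would honour all three. That is fair: the 22.6% shows what parity alone delivers, not what will happen. But the text does not define the list, and a shuffle leaves the zone problem at 93.1%. The process figure was not available to this review and might show more.

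Third, a reader might take "the eligible participants will be randomised at a 1:1 ratio to one of the two arms" to mean that the unit of randomisation is misstated. It is not. The same sentence ties allocation to the participant's PIA, and the participant recruitment section keeps each PIA in one arm.

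Fourth, pairing by zone removes only differences between zone averages. Table 1 puts between two and eight states in a zone, so two PIAs in one zone may still differ considerably. The gain in precision is therefore unknown, and a compulsory zone fixed effect could lose power. This also stands, and it is why the analysis model is kept out of the recommendation.

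**Conclusion.** The point holds as an avoidable weakness in a stated method. The rule has no zone restriction, although the design supplies exactly two PIAs per zone, and it yields 6:6 only under a property of the list that the text does not state. The consequences are:

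- a 22.6% chance of exactly 6:6 if parities are independent;
- if 6:6 is forced, a 93.1% chance that at least one zone sits wholly in one arm, with 2.73 of six expected.

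These probabilities are exact and need no assumption beyond the reading of the list. The effect on the result is chance imbalance and possible loss of precision with 12 clusters. Its size depends on how far zones differ, which the article does not quantify. It is not bias in expectation.

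**What to change.** Replace the odd/even sentence under Randomisation and blinding with:

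> Within each of the six zones, one of the two consenting PIAs is randomly assigned to intervention and the other to control, all six assignments generated together after baseline is complete.

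This needs six draws instead of one list, and no extra sites, participants or money. It fits the existing plan to allocate after baseline. It must be in place before allocation.

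Decide separately whether the analysis fits zone as a fixed effect. That costs 5 df and pays only if zone explains roughly 25–31% or more of between-PIA variance at assumed ICCs of 0.05–0.02 (about 40% at 0.01). The change to the allocation does not depend on that choice. In the same edit, reconcile the count of PIAs per zone in Study location with the two per zone in the cluster recruitment section.

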### Design measures to avoid bias

The allocation codes will be concealed by the use of a computer-generated random number list. The principal investigator, the trial team, trial manager or staff members will be blind to the allocation codes during the trial. The control arm will also receive general enquiry phone calls that will further help in masking the allocation. To avoid contamination, we will physically separate the intervention team and the control team and blind the telephone support person (staff) about which arm they belong to. We believe the lockdown and work from home will assist in masking. Separate staff will make the phone calls in the intervention and control arms.

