### Training of the staff

The expert resource persons will train the chief executive officer and the chief operating officer/state programme manager from the six selected PIAs (12 in total) on the intervention manual’s content, process and strategies. Training of trainers will be given to 36 facilitators, six members each from 6 intervention PIAs and the State Rural Livelihood Mission (SRLM) from the selected states. A virtual master class will train these facilitators on providing the intervention (telephonic befriending). This training will last for approximately 6 h and will include a session on question and answers. Following this training, the training video, protocol booklet and frequently asked Q&As will be shared with the facilitators. Additionally, an online support centre will be set up for continuous support to the trainers.

The trained facilitators will train 6 PIA staff (two from each agency) and each trained PIA staff will train an average of 6 other staff members. Staff who are a part of the DDU-GKY project for 1 year or longer will be trained to deliver the intervention. Staff who are a part of the intervention team will only receive this training on the intervention module. These trained staff members will reach out to 720 DDU-GKY alumni through this intervention.

Each befriender will be allocated between 10 and 15 students in their PIA. A 6-h virtual training is designed for the staff, covering the components to be delivered during each session. An intervention manual for the training has been developed, which was also translated into the local language. After the training, the trained staff will be provided with the intervention manual, an online video of the training session with subtitles, audio clips of sample interview content and a module on frequently asked questions. The intervention manual includes guidelines on developing a relationship with the client, introduction and orientation of participant to befriending, management of participant distress, confidentiality and safety issues for both staff and participants. In addition to the virtual training, befrienders will be monitored frequently through the online support centre to ensure fidelity to the intervention protocol.

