**Fig. 2 Fig2:**
[figure not shown]
Process of the trial

During the telephone calls, a semi-structured questionnaire will be used to gather information on the stressors and risk factors in the context of this pandemic outbreak. Telephonic conversations will be recorded with the consent of the participants and later transcribed by the research team. The specific domains that will be assessed include the situational stressors in the context of the COVID-19 outbreak and the different support mechanisms available to manage the difficulties. The staff will be trained to encourage the participant to speak about their issues and difficulties in the present context and empathetically listen to their worries.

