### Data entry and data management

The online data collection tool was developed and linked to the dedicated server in the research centre. The participant will enter the data directly to the online mobile portal, uploading the data directly onto the research server. The stored data set and codes will be protected using a password by the trial manager, independent of the trial team. The centrally stored data will be cleaned and analysed by the research team under the supervision of the trial manager, and the trial manager will verify the results independently to ensure the accuracy of the results. Data will be de-identified to ensure the confidentiality of information. Significant findings of the study will be reported in scientific journals and will be presented in conferences and workshops. Interested researchers can contact the principal investigator for further research collaborations.

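### The trial manager and the callers are declared blind, but the tasks the article gives them make that impossible, and the allocator also supervises the analysis

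*Protocol article*

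**What the plan says.** Design measures to avoid bias (protocol article) makes two blinding claims. The first is general: "The principal investigator, the trial team, trial manager or staff members will be blind to the allocation codes during the trial". The second concerns the callers: each telephone support person is to be kept unaware of the arm they work in, helped by physical separation of the two teams and by home working.

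Other sections assign the tasks:

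- **Allocation.** Randomisation and blinding has participants randomised "to one of the two arms (intervention or control) by the trial manager based on the PIA to which they belong". A computer technician creates the random list, and the section gives its key: "odd numbers on the list will be allocated to the intervention arm, and the even numbers will be allocated to the control arm".
- **Delivery.** Training of the staff describes a 6-h virtual course, a manual, a video and sample audio for the befrienders, and says: "Staff who are a part of the intervention team will only receive this training on the intervention module". The same section states that control callers are separate people with no specific training.
- **Calls.** Both arms get four calls. Befriending calls run through three structured phases and last 30 min to 1 h. Control calls are general enquiries lasting 5 to 30 min.
- **Transcription.** The description of the intervention arm says: "Telephonic conversations will be recorded with the consent of the participants and later transcribed by the research team".
- **Analysis.** Data entry and data management has the data "cleaned and analysed by the research team under the supervision of the trial manager", after which the trial manager checks the results, in a step described as independent.

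**The concern.** A blinding statement tells the reader which sources of bias the design has closed off. Here two of the roles named as blind are given work that cannot be done without knowing the arm.

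Two consequences follow. First, a report that repeats this statement would credit the trial with masking of the trial manager and the callers that could not have occurred. Second, the person who allocated the PIAs would oversee data cleaning and analysis and then certify the results. WHO-5, PHQ-9 and MSPSS are all self-reported scales. The article plans odds ratios from logistic regression on the outcomes, so scale scores have to be turned into categories at some point. Decisions of that kind, if still open when the data are seen, are where knowledge of the arm could do harm.

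**Working it through.** No figure in the article bears on this point, so the check sets each blinding claim beside the tasks given to that role.

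**1. Trial manager**

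- Claim: blind to the allocation codes during the trial.
- Task: randomises "by the trial manager based on the PIA to which they belong", using a list on which odd means intervention and even means control.
- Reasoning: whoever applies that list to PIAs learns the arm of each PIA in doing so. Allocation takes place within the trial, after baseline, so reading the claim as limited to the trial period does not help. Reading it narrowly, as concealment of the list alone, does not help either, because this is the person who uses the list.
- Further tasks: supervises cleaning and analysis, then verifies the results. A check by the person who allocated and supervised is not independent in the usual sense.
- Result: contradicted.

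**2. Callers**

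- Claim: blind to the arm itself, not merely to a code.
- Tasks, by arm:

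| | Intervention callers | Control callers |
|---|---|---|
| Training | 6-h course, manual, video, audio samples | none specific |
| Content | three structured befriending phases | general enquiry, COVID-19 information |
| Call length | 30 to 60 min | 5 to 30 min |
| Total over four calls | 4 × 30 = 120 to 4 × 60 = 240 min | 4 × 5 = 20 to 4 × 30 = 120 min |

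- Reasoning: the two ranges touch only at 30 min per call (120 min in total). Training and content do not match at all. A caller trained from an intervention manual that covers introducing the participant to befriending knows that befriending is what they deliver.
- Result: contradicted.

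**3. Research team**

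- Tasks: transcribes recorded calls, and cleans and analyses the data. Both are stated.
- Reasoning: a befriending call shows its arm by its content. If the same individuals do both jobs and can link a call to a PIA, they know the arm of that PIA.
- Result: a route by which analysts could be unmasked, not a demonstrated unmasking.

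**4. Reach of one disclosure**

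- Recruitment of participants within PIAs puts everyone from a PIA in one arm, with 120 per PIA.
- 12 × 120 = 1440 participants and 6 × 120 = 720 per arm, both as stated in the article.
- One PIA's arm therefore reveals the arm of 120 participants, or 120/1440 = 8.3% of the sample. This describes how far a disclosure spreads. It is not an estimate of bias.

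**The case against.** The strongest reply is that the blinding statement should not be dismissed as a whole, and that is right. A reader might infer from the two contradictions that no blinding exists in this trial. The article does not support that, for these reasons:

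- No allocating, delivering or analysing task is given to the principal investigator, so the claim for that role is not contradicted.
- The control calls are meant to help mask the allocation and may partly mask participants. Nothing here shows that participants are unmasked.
- The statement "The stored data set and codes will be protected using a password by the trial manager, independent of the trial team" sits in a data-security paragraph that goes on to de-identification. Those codes are not shown to be the allocation codes. The trial manager point rests on the act of randomising and does not need this sentence.
- The research team is nowhere equated with the trial team that is declared blind, so transcription does not contradict a stated claim. Recording is described only under the intervention arm, and nothing says transcripts are linked to outcome records.
- Outcome assessors are not named as blind, but they may belong to the trial team, and a condensed article may leave this to the full protocol. That is not a finding.
- A PIA identifier reveals the arm only to someone who knows that PIA's allocation. Cut-points and models may be fixed in an analysis plan that is not shown. So one cannot say that analysts would know the arm or would choose with knowledge of it, only that they could.

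Two safeguards also deserve credit. Allocation follows baseline assessment of all participants, which protects enrolment from knowledge of the arm. Participants enter their own data, which limits assessor influence, although the article also describes follow-up as carried out by telephone.

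On the callers, it can be said that untrained control callers might not realise that another arm exists. That is possible, but the claim covers all telephone staff, and it fails for the trained befrienders.

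None of this removes the contradictions for the trial manager and the callers.

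**Conclusion.** The point stands for two roles. The stated blinding of the trial manager and of the callers is wrong as written, and this is a conflict between sections of the same article, not a detail left to another document. It should be corrected.

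That the trial manager both allocates and oversees the analysis creates an avoidable opening for bias in the handling of self-reported outcomes. Transcription and analysis by one research team is a second, weaker opening. It rests on two assumptions that the article neither confirms nor excludes: that the same individuals do both jobs, and that calls can be tied to PIAs.

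The size of any bias cannot be computed from the document. Confidence is high for the two contradictions and lower for any effect on the results.

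**What to change.** 1. Have the computer technician, who already creates the list, apply it to the PIAs and hold the key. Alternatively, leave allocation with the trial manager and give supervision and verification of the analysis to someone else. NIRDPR is a poor choice as key holder because it selects and invites the PIAs, so cluster recruitment and allocation would then be in the same hands.
2. Supply the analysis file with recoded PIA identifiers and arms labelled A and B until cleaning is closed and the analysis code is locked.
3. Where existing staffing allows, keep those who transcribe calls from analysing outcome data before that lock. The article does not give the size of the research team, so this may not be free.
4. Delete the claim that callers are blind to their arm, and the claim for the trial manager if that role still allocates. Keep the claims that the assigned tasks do not contradict.

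The cost is a minor reassignment of tasks among roles already in the plan and a blinding statement that is less favourable but true. Sample size, outcomes and delivery of the calls are unaffected.
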